#### h. Interaction with other products

rTMS treatment must be avoided in patients with implants which are close to the scalp, such as cochlear implants or neurostimulators. The TMS safety questionnaire is designed to identify such cases.

rTMS treatment poses an increased risk of inducing an epileptic seizure in case of an interaction with products with a significant seizure-threshold-lowering potential. These have been well-described in TMS guidelines.

#### i. Predictability of effect

In the phase II trial, we included a broad range of patients with a first-ever ischemic stroke or intracerebral hemorrhage that resulted in unilateral upper extremity paresis. A meta-analysis shows that treatment efficacy is higher when treatment is started within the first month post-stroke with a mean difference of 9.3 points on the Fugl-Meyer Upper Extremity, compared to a mean difference of 1.14 points between 1 and 3 months and after 3 months post-stroke.

#### j. Can effects be managed?

cTBS treatment has a risk of 0.02% per cTBS session of inducing an epileptic seizure. This was not observed in our phase II trial. The consequences of inducing an epileptic seizure can be mitigated by adequate training of personnel. Other side effects of cTBS treatment are minor (headache, muscle pain) and wear off within a few hours.

### **13.2 Synthesis**

Data from our phase II trial (B-STARS) shows that cTBS treatment leads to a clinically relevant improvement in upper limb recovery, with 17% (n = 60; 9.6 points; 95%CI 1.2–17.9) additional recovery of upper limb activity, as measured with the ARAT three months after stroke. This additional recovery led to a significant improvement in activity and participation (of similar magnitude) and a reduction in the length of stay at the rehabilitation center by 18 days on average.

cTBS treatment only led to mild side effects, such as headache (<4%) and muscle pain (<1%) and was reported to be tolerable and comfortable. The risk of inducing an epileptic seizure is rare (0.02%) and consequences of an epileptic seizure can be mitigated by adequate training of personnel.

In conclusion, the potential benefits of cTBS treatment are substantial and the potential risks are minor and manageable.

|                                                                                                                                                                                                                                                                                                                                          |                                                                                                                                                                                                                                                                                                                                                                         |                                                                                                                                                                                                                 |
|------------------------------------------------------------------------------------------------------------------------------------------------------------------------------------------------------------------------------------------------------------------------------------------------------------------------------------------|-------------------------------------------------------------------------------------------------------------------------------------------------------------------------------------------------------------------------------------------------------------------------------------------------------------------------------------------------------------------------|-----------------------------------------------------------------------------------------------------------------------------------------------------------------------------------------------------------------|
| Cardiac
Angina
Arrhythmia
Atrial fibrillation
Angina pectoris
Bradycardia
Cardiac arrest
Cardiomyopathy
Heart failure
Myocardial infarction
Tachycardia                                                                                                                                             | Pulmonary
Aspiration
Bronchitis
Chronic obstructive pulmonary disease
Dyspnea
Obstructive sleep apnea
Oxygen desaturation
Pneumonia
Pulmonary embolism
Respiratory failure / arrest
Respiratory tract infection                                                                                                                    | Gastro-intestinal
Constipation
Dysphagia
Fecal incontinence
Gastro-intestinal hemorrhage
Ileus
Melena
Mucosal irritation
Nausea
Rectal hemorrhage
Stress ulcer
Vomiting |
| Central nervous system
Delirium
Depression
Epileptic seizure
Headache
Hydrocephalus
Recurrent ischemic stroke
Recurrent intracerebral hemorrhage
Recurrent stroke
Retinal ischemia
Sleep disorder
Status epilepticus
Spasticity
Transient ischemic attack
Transient monocular blindness | General / other
Anemia
Arterial hypertension
Arterial hypotension
Deep vein thrombosis
Dehydration
Fall (and consequences)
Fatigue
Fever
Hematuria
Hip fracture
Hyperglycemia
Infections
Pain
Pressure sore
Renal failure
Sepsis
Syncope
Undernutrition
Urinary incontinence
Urinary tract infection |                                                                                                                                                                                                                 |

**Appendix C – Trial organisation**

The Executive committee of the trial consists of the trial's central PIs and coordinating investigators. They meet regularly, discuss trial progress and prepare information for the Steering committee.

## 1. Study objectives

Primary Objective:

- To assess whether 10 sessions of cTBS of the contralesional primary motor cortex (M1) combined with regular care upper limb training, started within three weeks after stroke onset and continued every working day for two weeks, reduce upper limb impairment at 90 days after stroke, compared to sham stimulation.

Secondary Objective(s):

To assess whether 10 sessions of cTBS of the contralesional M1 combined with regular care upper limb training, started within three weeks after stroke onset and continued every working day for two weeks:

- improve upper limb activity, manual dexterity and quality of life, and reduces disability and dependence at 90 days and 12 months after stroke, compared to sham stimulation;
- reduce upper limb impairment at 12 months after stroke, compared to sham stimulation;
- are cost-effective compared to sham stimulation;
- reduce excitability of the contralesional M1 during the 2-week treatment period, compared to sham stimulation;
- increase ipsilesional M1 excitability after 10 treatment sessions, compared to sham stimulation.

## 2. Study design

B-STARS2 is a multi-centre, double-blind, randomised, sham-controlled, clinical trial.

Participants will be recruited from 16 rehabilitation centres in the Netherlands over a period of 51 months (Q2 of 2024 to Q4 of 2028). The total duration of follow-up for each participant is until one year after stroke. The total study duration is 63 months.

Baseline assessment will be performed before the start of the intervention, which must occur within 21 days after stroke onset. Follow-up assessments will be performed at 90 days (+/- 7 days) and 12 months (+/- 14 days) post-stroke (Figure 1).

The intervention consists of ten daily sessions of active or sham cTBS, delivered over the contralesional primary motor cortex, started within 21 days post-stroke and combined with regular care upper limb therapy.

Participants are randomly assigned in a 1:1 ratio to one of the two treatment groups (group A or B) using a web-based data management service. Treatment allocation is stratified by rehabilitation centre and the ability to extend one or more fingers of the affected hand.

An independent DSMB is monitoring the safety of participants of the trial. The DSMB meets at least annually. An independent statistician will perform unblinded interim analyses on all reported (serious) adverse events after 150 and 300 patients have completed the 90 days post-stroke follow-up. The independent statistician will report the outcome of the interim analyses directly to the DSMB, as well as listings of all SAE reports and unblinded aggregate summaries of data by treatment group for review in closed meetings. Feedback, blind to treatment, will be provided in written conclusions to the B-STARS2 project leaders.

[figure not shown]

**Figure 1.** Study timeline.

### 3. Primary outcome

The primary outcome is the score on the Fugl-Meyer Upper Extremity Assessment (FM-UE) at 90 days post-stroke (Table 1). The FM-UE is a reliable and valid motor performance test consisting of 33 tasks that assesses upper limb motor impairment on a scale from 0 to 66 points, with a higher score indicating less impairment. The FM-UE will be assessed by certified assessors. Before

certification, assessors will receive on-site training by the team of coordinating investigators and must successfully complete an FM-UE exam.

## 4. Secondary outcomes

Secondary outcomes are the score on the FM-UE at 12 months post-stroke and scores on the Action Research Arm Test, Nine Hole Peg Test, modified Rankin Scale, Barthel Index, hand and participation sections of the Stroke Impact Scale, the EuroQol-5D-5L at 90 days and 12 months post-stroke. Additional secondary outcomes are length of stay in the rehabilitation centre, change in ipsilesional and contralesional excitability and cost effectiveness. Secondary outcomes are described in Table 1.

**Table 1.** Outcome assessments

| Assessment                          | Timepoint          | Description                              | Abbreviation |
|-------------------------------------|--------------------|------------------------------------------|--------------|
| Primary outcome              |                    |                                          |              |
| Fugl-Meyer – Upper Extremity        | 90 days            | Upper extremity impairment test          | FM-UE        |
| Secondary outcomes           |                    |                                          |              |
| Fugl-Meyer – Upper Extremity        | 12 months          | Upper extremity impairment test          | FM-UE        |
| Action Research Arm Test            | 90 days, 12 months | Upper extremity activity test            | ARAT         |
| Nine Hole Peg Test                  | 90 days, 12 months | Manual dexterity test                    | NHPT         |
| Modified Rankin Scale               | 90 days, 12 months | Disability and dependence questionnaire  | mRS          |
| Barthel Index                       | 90 days, 12 months | Activities of daily living questionnaire | BI           |
| Stroke Impact Scale – Hand          | 90 days, 12 months | Hand function questionnaire              | SIS-hand     |
| Stroke Impact Scale - participation | 90 days, 12 months | Participation questionnaire              | SIS-par      |

|                             |                                                                                          |                                                                                   |          |
|-----------------------------|------------------------------------------------------------------------------------------|-----------------------------------------------------------------------------------|----------|
| EuroQol - 5 dimensions      | 90 days, 12 months                                                                       | Quality of life questionnaire                                                     | EQ-5D-5L |
| Length of stay              |                                                                                          | Length of stay in the rehabilitation center                                       | LOS      |
| Contralesional excitability | Before the 1 st , 6 th and 10 th cTBS session           | Resting motor threshold of the contralesional M1                                  | cRMT     |
| Ipsilesional excitability   | Before the 1 st and 10 th cTBS session.                            | Resting motor threshold of the ipsilesional M1                                    | iRMT     |
| Contralesional inhibition   | Before and after the 1 st , 6 th and 10 th cTBS session | Ratio between the average motor-evoked potential amplitude before and after cTBS. | CI       |

## 5. Overall data and statistical analysis principals

The analysis and reporting of the trial will be in accordance with CONSORT guidelines. This statistical analysis plan (SAP) specifies: (i) Hypotheses to be tested; (ii) Treatment effects to be estimated in order to satisfy the primary and secondary objectives of this trial; (iii) Technical description of the statistical methodology and procedures for performing the statistical analysis of outcome measures and SAE data; (iv) Primary, secondary, and sensitivity analyses; and (v) Subgroup analyses. The SAP will be signed off by the trial Executive Committee and the trial statistician and then published. The final statistical analyses will be performed once recruitment has ceased, final follow-up has been completed, final data have been checked and any errors corrected, and the database has been locked.

### 5.1. Blinding & data lock

Sham cTBS will be performed using a sham TMS coil, which looks identical to an active TMS coil but does not produce effective stimulation. The sham and active TMS coils will be labelled with a code (A/B) by the coordinating investigator who is not involved in any of the TMS treatments. The TMS therapist performs randomization and patients will be allocated to receive treatment with coil A or B, depending on their group allocation (A/B). Therefore, the TMS therapists and patients are

unaware of treatment allocation. Blinding of the patient and therapist will be maintained until the last patient has completed the final follow-up (at 12 months post-stroke).

Only one of the coordinating investigators can link treatment allocation to the active or sham condition. The independent trial statistician will combine data on treatment allocation with the clinical data to report to the data safety monitoring board (DSMB). The treatment allocation code will not be broken until the database has been locked, which is after the last patient has completed the final follow-up and all data have been cleaned. Cleaning of the data will be performed by a coordinating investigator who is unaware of treatment allocation.

## 5.2. Handling of missing data

Missing data due to loss to follow-up are assumed to be missing at random. Missing data will be reported. Prior to analysis, missing data is imputed using multiple imputation. Imputation will be performed using multiple imputation generating 500 datasets to account for inherent uncertainty, performed separately for each treatment group. This will be described in the results section of the manuscript.

## 5.3. Quality control

Before database lock and unblinding, summary tables will be verified, potential errors will be corrected if needed and full analyses will be performed based on dummy randomization codes. Statistical analyses, including R code, log and output will be peer reviewed to ensure accuracy of the analyses.

# 6. Primary estimand

Secondary endpoints will use a similar framework for the main estimand.

## 6.1. Patient population

The patient population is based on the intention-to-treat principle and consists of all subjects who are randomized to active or sham cTBS and started at least one cTBS session (ITT1), analysed according to the treatment group they were randomized to.

## 6.2. Primary endpoint

The primary endpoint is the change from baseline in FM-UE score at 90 days post-stroke.

### 6.3. Population level summary

The difference in the mean FM-UE change from baseline to 90 days post-stroke between active and sham cTBS.

### 6.4. Treatment condition

Active cTBS compared to sham cTBS.

### 6.5. Intercurrent event handling

Death: Missing data in case of death will be imputed with an FM-UE score of 0.

Treatment Discontinuation: Data collected after treatment discontinuation will be included and analysed according to the treatment group to which the participant was randomized, except if treatment was discontinued before the first cTBS session.

## 7. Analyses to be performed

### 7.1. Retention

We will provide a CONSORT flow diagram, reporting the number of patients who were randomized, treated, adhered to and completed follow-up by treatment group and report reasons for withdrawal.

### 7.2. Baseline data

We will summarize baseline characteristics per treatment group without formal statistical testing. The following will be presented: Age, sex, ethnicity, living arrangement, employment status, status at baseline (FM-UE, ARAT, NHPT, BI, mRS, SIS, EQ-5D-5L), NIHSS at hospital admission, time between stroke onset and start of cTBS, lesion type (ischaemic stroke or intracerebral haemorrhage, lesion location (cortical subcortical or brainstem), right hemisphere affected and dominant hemisphere affected), electrophysiological status (MEP presence), stratification factor (ability to extend one or more fingers), acute intervention, time between stroke onset and start of upper limb therapy and time between stroke onset and admission to rehabilitation centre, cardiovascular risk factors (diabetes mellitus, hypertension and smoking).

### 7.3. Adherence to allocated treatment

We will summarize the number of completed cTBS sessions per treatment group, descriptively.

### 7.4. Primary analysis

The primary outcome is the FM-UE score at 90 days poststroke. The FM-UE reflects upper limb impairment on an ordinal scale from 0 (maximum impairment) to 66 points (no impairment).

The primary analysis is performed using a linear mixed model. Analysis will be performed in the primary estimand, including all randomized subjects who started at least 1 cTBS session. The outcome variable is the FM-UE score at 90 days poststroke. The model includes fixed effects for baseline FM-UE score; stratification factor (ability versus no ability to extend one or more fingers), age, gender, stroke subtype (ischemic stroke vs. intracerebral haemorrhage) and treatment (sham cTBS; active cTBS) and random effects for rehabilitation centre.

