#### 4.4 Sample size calculation

The required sample size to test our hypothesis (superiority) in two groups is 440 subjects, based on a two-sided two-sample t-test power calculation with a minimal detectable effect of 6.6 points on the FM-UE scale (10% of the maximum score of 66, a mean score at 90 days of 42 and a standard deviation of 23 (calculated from the B-STARS trial data), a statistical significance level of 0.05 and statistical power of 0.85 (G\*power 3).

A study that specifically examined clinically important differences of FM-UE scores in stroke patients found that these ranged from 4.25 to 7.25 points, depending on the different facets of UE movement. A minimal clinically important difference of 6.6 points (10% of the maximum score FM-UE score) is in line with the module 'Noninvasive brain stimulation with rTMS' for the Dutch guideline 'Ischemic stroke and intracerebral hemorrhage'.

To compensate for possible loss to follow-up, we will include 454 patients. This sample size is also sufficient to demonstrate a treatment effect on secondary outcome measures. For example, for the ARAT, which tests upper limb-specific activity, a sample size of at least 396 would be required, based on a minimal clinically important difference of 5.7 and a mean score and standard deviation of 30 and 23, respectively (calculated from the B-STARS trial data), a statistical significance level of 0.05, and a statistical power of 0.8 (gigacalculator.com).

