## 7.7. Subgroup analyses

Predefined subgroup analyses will be based on baseline FM-UE extremity score (FM  $\leq$  20 versus FM  $>$  20); stroke subtype (ischemic stroke versus intracerebral haemorrhage); stroke location (cortical versus subcortical versus brainstem) and time to start of treatment (within 14 days versus 15 to 21 days). These analyses will be performed by including an interaction term between treatment and the previously described parameters in the linear regression model described in section 7.4.

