## 2.5. Time

On average, stroke patients spend 8 to 12 weeks in clinical rehabilitation and recover around 70% of lost function within the first 3 months after stroke. Subsequently, patients spend an average of 3 months in outpatient rehabilitation. Thereafter, patients reintegrate into society and if applicable, reintegrate into the workforce. We will extrapolate the quality of life and costs at one-year post-stroke over longer periods of time to investigate the potential impact on long-term cost-effectiveness. At one-year post-stroke, most patients

have completed rehabilitation and recovery will have plateaued. Therefore, we will perform a scenario analysis with a time horizon of the cost-utility analysis of one year after stroke.

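### The primary model leaves out time since stroke, although baseline FM-UE can be taken on any day up to day 21; the cost is a small, avoidable loss of precision, not bias

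*Combined protocol and SAP*

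**What the plan says.** SAP 2 (and protocol 3) place the baseline assessment before the first cTBS session, which must fall within 21 days of stroke. No earliest day is given. The primary assessment is due 90 days after stroke, with a 7-day margin either side; it is not counted from baseline.

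For the primary analysis, SAP 7.4 states: "The model includes fixed effects for baseline FM-UE score; stratification factor", followed by age, gender, stroke subtype and treatment, with random effects for centre. Protocol 10.2 presents its own covariate list as a minimum and does not name time since stroke either. Randomisation is stratified by centre and finger extension only.

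The interval itself is available. Protocol 8.1.3 records the date of stroke onset and protocol 8.3 the date of each session. SAP 7.2 tabulates "time between stroke onset and start of cTBS" by arm, and SAP 7.7 uses it as a subgroup factor: "time to start of treatment (within 14 days versus 15 to 21 days". SAP 7.6 allows an unbalanced baseline characteristic to be added to the 7.4 model in an optional sensitivity analysis.

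On the pace of recovery, section 2.5 of the health-economic plan says that patients "recover around 70% of lost function within the first 3 months after stroke".

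**The concern.** If recovery is steep in the first weeks, a baseline score means different things on different days. A patient who scores 20 on day 7 has more of the recovery period left than one who scores 20 on day 21, and would be expected to score higher at day 90. The 7.4 model gives both the same expected outcome if they match on centre, finger extension, age, gender and subtype.

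Two things are at stake. Variation that could be explained stays in the residual, so the standard error is larger than it need be. And if the arms differ by chance in timing, the primary estimate is not corrected for it. The plan already treats timing as relevant, since it tabulates the interval and tests it as an effect modifier.

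**Working it through.** **1. The plan's sample size.** Protocol 4.4 uses a "two-sided two-sample t-test power calculation" with "a minimal detectable effect of 6.6 points on the FM-UE scale", SD 23 and "a statistical significance level of 0.05 and statistical power of 0.85". The standardised effect is 6.6/23 = 0.287. The t-test needs 219.03, so 220 per arm and 440 in all. Then 440/0.97 = 453.6, which rounds up to 454. Both figures reproduce. No covariates enter this calculation, so the omitted term does not affect it.

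**2. How far prognosis differs by day (assumed curve).** Suppose a share 0.7 × ln(1+t)/ln 91 of the initial loss has been regained by day t, which gives 70% at day 90. For baseline score b on day t:

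66 − FM90 = (66 − b) × 0.3 / (1 − 0.7 × ln(1+t)/ln 91)

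- b = 20, day 7: 46 × 0.3/0.677 = 20.4, so FM90 = 45.6.
- b = 20, day 14: FM90 = 42.2.
- b = 20, day 21: 46 × 0.3/0.520 = 26.5, so FM90 = 39.5.

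The slope at b = 20 is 6.1/14 = 0.44 points per day. It is proportional to (66 − b): the gap between day 7 and day 21 is 7.5 points at b = 10 and 3.5 at b = 40. An exponential curve with a 30-day constant gives 5.6 points at b = 20.

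**3. Precision.** With days uniform over a window, SD(days) = width/√12. The gain in effective sample size is (slope × SD of days)² / residual variance. Assumed residual SDs are 16.4, which is 23 × √(1 − 0.7²), and 12, which corresponds to a baseline correlation of about 0.85.

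| Case | Slope per day | SD of days | Residual SD | Gain |
|---|---|---|---|---|
| Low: days 10–21, baseline averaging 30 | 0.32 | 3.18 | 16.4 | 1.04/269 = 0.4% |
| Middle: days 7–21, baseline 20 | 0.44 | 4.04 | 16.4 | 3.16/269 = 1.2% |
| High: days 5–21, baseline averaging about 23 | 0.42 | 4.62 | 12 | 3.76/144 = 2.6% |

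If every patient had baseline 20, the high case would be about 3.0%. A wider grid without any curve (slope 0.25 to 1.0 per day, correlation 0.5 to 0.8, days from 3 or 7 to 21) gives 0.3% to 14%; the top figure needs every input at its extreme.

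In power terms, take slope 0.5, days 7–21 and correlation 0.7. The standard error falls from 1.566 to 1.554. Power for 6.6 points goes from 0.988 to 0.989, and for 4.25 points (the lower end of the range cited in protocol 4.4) from 0.775 to 0.781.

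**4. Chance imbalance.** With days 7–21 and 220 per arm, the arm difference in mean days has SE 4.04 × √(2/220) = 0.385. Its 95% limit is 1.96 × 0.385 = 0.755 day, which shifts the estimate by 0.755 × 0.44 = 0.33 points, or 5% of 6.6.

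**5. Validity.** In 4,000 simulated trials of 440 per setting, the model without days gave mean estimates of 6.61 and 6.62 for a true 6.6 at slopes 0.5 and 1.0. Type I error was 0.051 and 0.047, against 0.050 and 0.048 with days included.

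**6. The 7.7 subgroup model.** SAP 7.7 adds an interaction term to the 7.4 model, which has no main effect of time. Fitted literally, the prognostic difference between early and late starters loads onto the interaction. With days 7–21, mean days in the two categories differ by about 7, so at slope 0.34 (baseline averaging 30) the spurious interaction is about 7 × 0.34 = 2.4 points. Simulation with no true interaction (step 2 curve, baseline 5–55, residual SD 14, 440 patients) gave 2.3 to 2.6 points across runs and rejected in 22% to 27% of trials, falsely favouring early treatment. With time also entered as a main effect, rejection returned to about 5%.

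**The case against.** The strongest case against is that this is a choice, not an error. The model is prespecified and valid under randomisation. NIHSS and lesion location are also collected and also left out, and a reviewer can always name one more prognostic covariate. Timing is not ignored either: it is tabulated by arm, examined in 7.7, and open to adjustment under 7.6. The curve in step 2 is also not the plan's. The 70% figure is a general remark about lost function in the health-economic plan, and the only logarithmic assumption in the documents (section 6 of that plan) concerns quality of life.

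Most of this stands, and it sets the size of the point. It does not remove it. Time since stroke differs from other candidates because it determines what the baseline score means. The 7.6 route is optional, states no threshold for imbalance, depends on the data observed, and leaves the primary estimate unchanged.

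A reader might set the 6-point gap in step 2 beside the 6.6-point target and infer that the omission could hide or mimic the treatment effect. That does not follow. The gap is between two patients at opposite ends of an assumed window; the target is a difference between arm means. The comparable figure is the 0.3 points in step 4. A reader might also infer bias, inflated type I error or an inadequate sample size. Steps 1 and 5 rule these out.

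**Conclusion.** The point holds as a minor improvement. Time since stroke is absent from the primary model although the baseline day varies and the endpoint day is fixed. The loss is about 0.4% to 2.6% of effective sample size, with exposure to a chance shift of about 0.3 points at the 95% limit. These sizes rest on an assumed recovery curve, assumed uniform days and assumed residual SDs; the documents give no FM-UE slope by day, no distribution of baseline days and no baseline-to-90-day correlation. The primary analysis as written remains unbiased with correct type I error.

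The consequence in 7.7 is conditional: it arises only if the interaction is fitted without the main effect of time. Many analysts would add that term by default, but the SAP does not say so.

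**What to change.** - In SAP 7.4, add time from stroke onset to baseline assessment, in days, as a continuous fixed effect. Add the same term to the FM-UE and ARAT models in 7.5.
- The documents do not expressly list the baseline-assessment date as a recorded item. If it is not available, use the stroke-to-first-cTBS interval already tabulated under 7.2.
- In SAP 7.7, state that the time-to-treatment model contains the main effect of time as well as its interaction with treatment.

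The cost is one degree of freedom in each model and no new data. Protocol 10.2 gives its covariates as a minimum, so the addition creates no conflict, and it can be made while the allocation code is unbroken. The slope appears to vary with baseline score, so one linear term will not capture all of the timing effect; with gains this small, a more elaborate term is not needed.
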